#### Control Treatment

Similarly, the control group will receive a document containing an alphanumeric identification number and a link or QR code. The identification code will be used in the same way as it is used for the intervention group, allowing participants to complete the questionnaires at the baseline and follow-up stages. The QR code will instead direct participants to a printable educational brochure. This brochure represents the standard treatment. It was introduced following a study conducted in 2021 that demonstrated its efficacy in increasing patient compliance, self-care skills, and disease knowledge in patients with VLUs [15]. Since then, it has been routinely used to educate VLU patients in the study settings. The educational content in the brochure covers some of the topics presented in the educational videos but in a short form, such as the nature of venous ulcers, the available treatments and compression therapy, dressing management, potential risks and complications, and beneficial lifestyle changes. The brochure will contain both written text and illustrative images and will be available to participants throughout the duration of the study.

#### Baseline Questionnaires

Patients who meet the eligibility criteria and consent to participate in the study will be requested by the researcher to provide sociodemographic and health-related data, including age, gender, level of education, occupation, with whom they live, presence of private or family care, preexisting pathologies, smoking habits, presence of pain, venous ulcer–related information, and medication management. The researcher will input these data and the Pressure Ulcer Scale for Healing (PUSH) Tool 3.0 measurement scale into the REDCap platform using a tablet provided by the company. To ascertain the level of knowledge about the disease, the level of self-care, and the patient’s well-being, the patient will be required to complete, respectively, the validated Venous Leg Ulcer Knowledge (VLUK) measurement scale, the validated Venous Leg Ulcer Self-Efficacy Tool (VeLUSET) measurement tool, and the WOW-I scale, using the company’s or their own smart device.

#### Follow-Up

Once the baseline questionnaires have been completed, patients will be invited to view the educational intervention assigned to them. Subsequently, at 4-week, 3-month, and 6-month intervals, participants will be required to complete the same questionnaires as at baseline. The VLUK, VeLUSET, and WOW-I scales have been employed to permit a comparison of pretreatment and posttreatment scores. Additionally, the outpatient nurse will be assigned to evaluate the patient’s venous ulcer using the PUSH Tool 3.0.

The final follow-up is scheduled to occur 12 months after enrollment and will be conducted via a telephone interview. Patients will be asked whether the condition has healed and, if so, for how long. Additionally, patients will be asked whether the ulcer has recurred.

#### Setting and Data Collection Method

The study will be conducted in outpatient clinics located in a northern Italian region.

The data will be collected by the nurses of the outpatient clinics involved in the study. Their duties will include checking eligibility criteria, collecting sociodemographic and health data at baseline, distributing the paper containing the unique code and QR codes for accessing the educational intervention and for completing the other questionnaires, and entering the data into the PUSH Tool 3.0 at baseline and at each follow-up. The remaining questionnaires (VLUK, VeLUSET, and WOW-I) are to be completed by the participants themselves at the outset of the study and at each subsequent follow-up. Data collection forms will be accessible through the electronic case report form. Data will be collected anonymously via the REDCap platform on a smartphone or tablet provided by the company or the patient.

#### Monitoring and Data Management

The researcher will be responsible for the collection of data at the time of the enrollment of the patient, either directly or through adequately trained personnel. Furthermore, the researcher will provide guidance to the nurse on the correct collection of data during the follow-up period, specifically in relation to ulcer assessment and the patient’s exit from the study.

It is not possible to exercise control over the questionnaires completed by patients themselves, as they are completed anonymously. During outpatient visits, the nurse will remind the patient or caregiver to view the educational intervention at least once by scanning the QR code and to complete the questionnaires during follow-ups.

The management, processing, and statistical analysis of the data will be conducted by external parties in collaboration with the sponsor. These parties will retain the data only for the duration necessary to complete the tasks assigned to them.

### Outcomes Measures

#### Primary Outcomes

The 2 coprimary outcomes of this study are an improvement in patient knowledge about their disease (VLUK score) and improvement in self-care skills (VeLUSET score) at 4 weeks.

#### Secondary Outcomes

Secondary outcomes (descriptive) include (1) VLUK and (2) VeLUSET scores at 3 and 6 months, (3) the evaluation of the healing process (PUSH Tool 3.0 score), and (4) improvements in well-being (WOW-I score) at 1, 3, and 6 months.

Moreover, the number of VLU recurrences in participants and the number of patients with complete healing will be assessed at 12 months of follow-up.

The instruments used to investigate the primary outcomes and well-being are self-administered questionnaires, while the healing process will be evaluated by the nurse using the PUSH Tool 3.0. The questionnaires and tools will be administered at the beginning of the study and at subsequent follow-up points, as described below in the study timeline.

Finally, the presence of any recurrence and complete healing will be investigated at the 12-month follow-up point through a single question asked by the nurse via telephone. No specific tools will be employed. The previously described evaluations will be conducted in both the intervention and control groups (Figure 1).

**Figure 1. F1:**
[figure not shown]
Study flowchart. PUSH Tool 3.0: Pressure Ulcer Scale for Healing Tool 3.0; VeLUSET: Venous Leg Ulcer Self-Efficacy Tool; VLUK: Venous Leg Ulcer Knowledge; WOW-I: Well-Being of Wounds Inventory questionnaire.

#### Description of Questionnaires and Tools

##### Venous Leg Ulcer Knowledge

Patient knowledge about the disease will be assessed using the questionnaire developed for the study “Educational Interventions in Patients with Venous Leg Ulcer Patients” (VLUK) tool, a validated instrument in the Italian context [6]. The VLUK assessment tool comprises 15 multiple-choice questions, each with one correct answer, designed to evaluate the patient’s knowledge of VLU pathophysiology, treatments, and recommended lifestyle changes [15].

##### Venous Leg Ulcer Self-Efficacy Tool

Patients’ self-care skills will be assessed using the VeLUSET, which has been validated in the Italian context in another unpublished study [23]. This tool assesses 5 dimensions of self-care in people with VLUs. The tool comprises 30 items, which can be grouped into 5 areas: general self-care (5 items), daily self-care activities (12 items), normal living (4 items), skills development (6 items), and trauma avoidance (3 items) [16,24].

##### Well-Being of Wounds Inventory

Patients’ well-being will be evaluated using the WOW-I scale, which will be translated and validated in the Italian context.

This scale assesses the well-being of the patient with VLUs in relation to their overall quality of life, their social circumstances, and the specific experience of the wound. The scale comprises 2 subscales, the first of which includes 2 factors or categories and the second of which has 5 factors or categories, resulting in a total of 19 items, each evaluated using a Likert scale [25].

##### PUSH Tool 3.0

The healing process will be documented within the study using the PUSH Tool 3.0, introduced in 1997 by the National Pressure Ulcer Advisory Panel and demonstrated to be an effective method for monitoring the healing of venous ulcers [26]. The tool was selected for its simplicity, speed, and reliability in monitoring venous ulcer healing. It comprises 3 items: lesion size (length × width), exudate quantity (none, light, moderate, and heavy), and tissue type (necrotic tissue, slough, granulation tissue, epithelial tissue, and closed). The total lesion score is obtained by summing the single-item scores, which range from 0 to 17. A reduction in the total score is indicative of progress toward the healing process.

If a patient achieves complete healing before the conclusion of the study, they will be classified as a “healed patient” and contacted again via telephone for follow-up purposes.

### Validation of the Italian Version of the WOW-I Questionnaire

To psychometrically validate the Italian version of the WOW-I, patients will be invited to complete the WOW-I questionnaire, the “EuroQol-Visual Analog Scale” [27], and the well-being subscale of the “Cardiff Wound Impact Schedule” [2], at baseline and 1 week later. Internal consistency will be assessed using Cronbach α at both time points. Stability over time will be evaluated by mean differences in test-retest scores, particularly in relation to well-being levels assessed via the EuroQol-Visual Analog Scale. Convergent validity will be estimated by correlating WOW-I subscales with the Cardiff Wound Impact Schedule well-being subscale.

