#### Video Intervention

A document containing an identification number and QR codes or links will be provided to participants who have been assigned to the intervention group. The identification code, which the patient is required to retain and keep secret, is alphanumeric and random. The code is used by the participant to complete the questionnaires at baseline and during the follow-up periods, with the intention of guaranteeing anonymity. The QR codes and links serve the purpose of enabling the patient to access the 4 experimental educational videos. Patients assigned to this group will be required to access the videos via QR codes or links and view them after completing the baseline questionnaires or within the initial 7-day enrollment period. The educational intervention can be viewed in the outpatient nursing clinic after the visit, in a waiting room, with one’s own smart device or a device provided by the company, or at the participant’s home.

The videos may be viewed on multiple occasions during the study period. The outpatient nurse will issue a reminder to the patient to view the intervention at least once.

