### Study Timeline

The study will be conducted over a period of 1 year from the end of enrollment. After enrollment (t_0_), the investigator will administer the WOW-I questionnaire to the patient at 7 ± 2 days (t_1_) to verify the stability of the instrument, and then 3 other follow-up assessments are planned for the primary outcomes. The second follow-up evaluation (t_2_) is scheduled to take place 4 weeks after the educational video is delivered, with subsequent follow-up assessments (t_3_) at 3-month intervals and 1 at 6 months (t_4_). If a patient is healed before the end of follow-up, they will be classified as a “healed patient.”

Finally, a long-term telephone follow-up will be conducted 12 months (t_5_) after enrollment (Table 1).

**Table 1. T1:** Summary of time points, interventions, assessments, and data collected.

	Enrollment	Postallocation				Closeout
	t_0_	t_1_ (1 wk)	t_2_ (4 wk)	t_3_ (3 mo)	t_4_ (6 mo)	t_5_ (12 mo)
Enrollment						
Eligibility screen	✓					
Informed consent	✓					
Allocation	✓					
Interventions						
Intervention extra: video						
Intervention standard: brochure						
Assessments						
Sociodemographic factors	✓					
Health factors	✓					
PUSH Tool 3.0^a^	✓		✓	✓	✓	
VLUK^b^	✓		✓	✓	✓	
VeLUSET^c^	✓		✓	✓	✓	
WOW-I^d^	✓	✓	✓	✓	✓	
Ask if there has been healing or if there is a recurrence						✓

a PUSH Tool 3.0: Pressure Ulcer Scale for Healing Tool 3.0.

b VLUK: Venous Leg Ulcer Knowledge.

c VeLUSET: Venous Leg Ulcer Self-Efficacy Tool.

d WOW-I: Well-being of Wounds Inventory questionnaire.

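### A mean test-retest difference cannot by itself establish WOW-I reliability, and the retest comes after the education has been released

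*Protocol article*

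**What the plan says.** The protocol article, under Validation of the Italian Version of the WOW-I Questionnaire, has patients complete the WOW-I, the EuroQol-VAS and the Cardiff well-being subscale at baseline and one week later. The stability criterion is: "Stability over time will be evaluated by mean differences in test-retest scores", with the qualifier "particularly in relation to well-being levels assessed via the EuroQol-Visual Analog Scale". Two other psychometric analyses are named. One is "Internal consistency will be assessed using Cronbach α at both time points"; the other correlates the WOW-I subscales with the Cardiff subscale for convergent validity.

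Under Study Timeline, "the investigator will administer the WOW-I questionnaire to the patient at 7 ± 2 days (t_1_) to verify the stability of the instrument". Table 1 places this retest in a post-allocation column.

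The educational material is released before then. Under Follow-Up: "Once the baseline questionnaires have been completed, patients will be invited to view the educational intervention assigned to them". Under Video Intervention, video patients are asked to "view them after completing the baseline questionnaires or within the initial 7-day enrollment period". For controls, under Control Treatment: "The QR code will instead direct participants to a printable educational brochure".

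The WOW-I is also a secondary outcome at 1, 3 and 6 months. Secondary Outcomes labels these outcomes descriptive, and Statistical Analysis treats secondary analyses as exploratory.

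**The concern.** There are two separate problems, and the first does not depend on the second.

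1. **The statistic.** Test-retest reliability asks whether the same patient gets about the same score again. A mean difference asks only whether the group average moved. Individual rises and falls can cancel, so a value near zero fits a scale with poor reproducibility as well as one with good reproducibility.

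2. **The interval.** Between test and retest, both arms are given educational material, and it differs by arm. Well-being is an outcome that the trial hopes this education will improve. If the average does move, instrument drift and a real response cannot be told apart by the planned statistic.

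At stake is how much support the substudy gives to the Italian WOW-I, and through it to one descriptive secondary outcome.

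**Working it through.** The article gives no sample size, reliability target or margin for the substudy, so there is no stated figure to reproduce. The calculations below are illustrations. They assume bivariate normal scores with SD 1 at each occasion. Where a sample size is needed they use n = 144, the trial total (72 per arm); that this is the substudy size is an assumption.

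**Step 1: no shift, varying reliability.** Let r be the true test-retest correlation. The expected mean difference is 0 for every r. The SD of individual differences is √(2(1 − r)), so the 95% limits of agreement are ±1.96·√(2(1 − r)). A simulation with 3,000 runs per setting gave the ICC (two-way, single measure, absolute agreement) and the share of runs in which a paired test at the two-sided 5% level was significant:

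| r | Mean difference | Significant | ICC | Limits of agreement (SD) |
|---|---|---|---|---|
| 0 | −0.003 | 4.7% | 0.00 | ±2.77 |
| 0.3 | 0.003 | 4.6% | 0.30 | ±2.32 |
| 0.5 | 0.002 | 4.9% | 0.50 | ±1.96 |
| 0.7 | 0.001 | 5.6% | 0.70 | ±1.52 |
| 0.9 | 0.001 | 4.5% | 0.90 | ±0.88 |

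The mean difference does not separate the rows. The ICC and the limits of agreement do.

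**Step 2: do the other planned statistics fill the gap?** Cronbach α measures how far items agree within one occasion; computing it twice does not compare a patient's two scores. The Cardiff correlation compares two instruments. Neither is test-retest reliability.

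**Step 3: order of events.** Baseline WOW-I comes first, then release of the video or brochure, then the retest between day 5 (7 − 2) and day 9 (7 + 2). Video viewing may take place up to day 7. The material is therefore available in both arms before the retest, but some video patients could be retested on day 5 or 6 before they have viewed it. Exposure at retest is mixed.

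**Step 4: a reliable scale with an assumed shift.** Take between-patient variance 0.90 and error variance 0.10, so reliability is 0.90. A shift d common to all patients adds occasion variance d²/2 to the denominator of the absolute-agreement ICC:

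- d = 0.1: 0.90 / (1 + 0.005) = 0.896
- d = 0.2: 0.90 / (1 + 0.020) = 0.882
- d = 0.3: 0.90 / (1 + 0.045) = 0.861

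The consistency ICC leaves the occasion term out: 0.90 / (0.90 + 0.10) = 0.90 for every d.

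For the mean difference with n = 144, the standard error is √(0.20/144) = 0.037. At d = 0.1 the ratio is about 2.7, and the simulation gave a significant result in 76% of runs. With 0.2 SD in the video arm and 0.1 SD in the brochure arm the figure was 98%; with 0.2 SD in both arms it was 99.9%. The simulated absolute-agreement ICC stayed at 0.88 to 0.89 in these three settings. The percentages hold only if stability were judged by a 5% significance test, which the article does not say.

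**Step 5: what arm-wise estimation does.** If every patient in an arm shifts by d, the absolute-agreement ICC computed within that arm still contains d²/2: at d = 0.3 it is again 0.90/1.045 = 0.86. Centring on the arm mean alone leaves the shift in as well. Only the consistency form, or centring by arm and occasion, removes it. Estimating within arm deals with a shift that differs between arms.

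**The case against.** The best defence is the qualifier "particularly in relation to well-being levels assessed via the EuroQol-Visual Analog Scale". It ties the WOW-I change to a concurrent health rating and may mean that stability is read among patients whose rating did not change. That is a partial safeguard against mistaking real change for instability. It does not settle the matter: no rule says who counts as unchanged, arm is not mentioned, and even in unchanged patients a mean difference does not measure reproducibility.

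A reader might infer that the mean difference carries no information on reliability. That goes too far. Systematic shift is one component of absolute agreement, and paired differences reported with their SD would yield the standard error of measurement and limits of agreement. The article does not promise that SD, so the accurate criticism is that the mean difference is insufficient alone.

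A reader might also infer that an education effect will be read as instability. The documents do not show this. They give no one-week effect; improvement is looked for at 1, 3 and 6 months, and some patients may be retested before viewing. An ICC of 0.86 fails no threshold in the article, because none is stated.

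Nor do the documents support the reading that a verdict of stable or unstable would be unfounded either way, with the trial's use of the WOW-I depending on it. No such dichotomy is described, and the substudy is presented as a parallel project.

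Finally, leaving the detail to an unseen analysis plan is no answer here: the article names its stability statistic, so this is a stated choice.

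**Conclusion.** The point holds in limited form. The named criterion cannot establish test-retest reliability on its own: Step 1 shows the same result at correlations of 0 and 0.9. This part needs no assumption about a treatment effect or about the substudy's size. The second part, that a shift may partly reflect the education, follows from the schedule as a possibility. Its size is unknown, and the 0.1 to 0.3 SD shifts are illustrations. The consequence is confined to the validation substudy and to the support for a descriptive secondary outcome. The retest comparison does not enter the coprimary VLUK and VeLUSET analyses or the randomised comparison of WOW-I scores.

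**What to change.** Amend the stability sentence in the validation section as follows:

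- Keep the mean test-retest difference, labelled as a measure of systematic shift.
- Make the stability criterion an intraclass correlation coefficient with its 95% CI, together with the standard error of measurement and limits of agreement.
- Compute these in patients who meet a prespecified EuroQol-VAS no-change rule between baseline and the one-week retest.
- Estimate within each randomised arm. Report the consistency form (or scores centred by arm and occasion), which removes a uniform shift within arm, alongside the absolute-agreement form, which retains it. A gap between the two shows the size of the shift.

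A sensitivity analysis in video patients with no views before the retest should not be added unless dated view counts are available at that time. Experimental Treatment promises only the number of views, and no view tracking is described for the brochure. As patients are reminded to view, the subset would probably be small and self-selected.

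No new data are needed for the main change, since both instruments are already collected at both times, and enrolment had not begun when the article was submitted. The cost is wider intervals, because estimates are made by arm and in stable patients only. A shift that varies between patients within an arm, as mixed viewing could produce, would still count as error in both forms of the coefficient.

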### Study Timeline

The study will be conducted over a period of 1 year from the end of enrollment. After enrollment (t_0_), the investigator will administer the WOW-I questionnaire to the patient at 7 ± 2 days (t_1_) to verify the stability of the instrument, and then 3 other follow-up assessments are planned for the primary outcomes. The second follow-up evaluation (t_2_) is scheduled to take place 4 weeks after the educational video is delivered, with subsequent follow-up assessments (t_3_) at 3-month intervals and 1 at 6 months (t_4_). If a patient is healed before the end of follow-up, they will be classified as a “healed patient.”

Finally, a long-term telephone follow-up will be conducted 12 months (t_5_) after enrollment (Table 1).

**Table 1. T1:** Summary of time points, interventions, assessments, and data collected.

	Enrollment	Postallocation				Closeout
	t_0_	t_1_ (1 wk)	t_2_ (4 wk)	t_3_ (3 mo)	t_4_ (6 mo)	t_5_ (12 mo)
Enrollment						
Eligibility screen	✓					
Informed consent	✓					
Allocation	✓					
Interventions						
Intervention extra: video						
Intervention standard: brochure						
Assessments						
Sociodemographic factors	✓					
Health factors	✓					
PUSH Tool 3.0^a^	✓		✓	✓	✓	
VLUK^b^	✓		✓	✓	✓	
VeLUSET^c^	✓		✓	✓	✓	
WOW-I^d^	✓	✓	✓	✓	✓	
Ask if there has been healing or if there is a recurrence						✓

a PUSH Tool 3.0: Pressure Ulcer Scale for Healing Tool 3.0.

b VLUK: Venous Leg Ulcer Knowledge.

c VeLUSET: Venous Leg Ulcer Self-Efficacy Tool.

d WOW-I: Well-being of Wounds Inventory questionnaire.

### Sample Size Calculation

The primary end points are the mean differences in pre-post scores (collected after 4 wk of follow-up and at baseline) of the VLUK and the VeLUSET questionnaires, which are considered coprimary hierarchical end points. This implies that the mean difference in VLUK within the treatment group must be statistically greater than the mean difference in the control group before the mean difference in VeLUSET between the control and treatment groups is evaluated. An interim analysis has been planned at the halfway point of the enrollment. The interim analysis assumes the Lan-DeMets O’Brien-Fleming approximation alpha-spending function and includes an early efficacy stop in case *Z*>2.54. The nominal *P* values are .006 and .048 at the interim and final analyses, respectively. Moreover, the conditional power will be calculated, and resampling will be performed in case of 50%<conditional power<80%. Otherwise, the sample size will be kept at the original size (72 patients per group), as described in the following. Particularly, a type I error of 5%, a power of 80%, and a dropout rate of 10% have been considered for the sample size estimation.

